#### Action protocol in the event of an alarm or if a professional assessment is requested

The protocol to be followed when an alarm sounds or when a practitioner is requested to come assess the newborn is shown in Fig. 2 (“Action protocol when an alarm sounds or a professional assessment is requested”).

**Fig. 2 Fig2:**
[figure not shown]
Action protocol when an alarm sounds or a professional assessment is requested

Table 3 shows the data that will be collected when visiting the newborn for an assessment. The mother’s and newborn’s positions will be documented according to a series of model images created for each degree of inclination (Fig. 1; “Models for mother’s and newborn’s positions for 15° and 45° inclination”).

**Table 3 Tab3:** Data recorded in case of alarm or if a professional assessment is requested

a. Number of alarms for this patient	
b. SO_2_, HR, and time	
c. Minimum SO_2_ during the episode and corresponding HR	
d. Minimum or maximum HR as appropriate and corresponding SO_2_	
e. Time to once again reach an SO_2_ > 90%	
f. Position of the mother and child	
g. Probable corresponding factor	
h. Child’s clinical situation	
i. If it entails terminating the procedure	
j. Possibility of airway obstruction in the child	

The practitioner will classify the alarm as clinical or nonclinical depending on whether the events that justify these alarms are clinical (CEs) or nonclinical events (NCEs), respectively. The CEs can, in turn, be clinically relevant (CREs) or nonclinically relevant events (NCREs).

NCEs do not entail that the intervention is terminated and can occur due to excessive ambient light, problems with the pulse oximeter’s connection cable or sensor, low battery levels, interference, and lack of system connectivity or availability.

The CEs include an SO_2_ < 91%, a HR > 180 bpm or < 111 bpm, and a newborn with symptoms. The protocol to be followed when clinical alarm sounds is shown in Figs. 3 and 4 (Fig. 3, action protocol when a SO_2_ < 91% clinical alarm goes off; Fig. 4, action protocol when a HR > 180 or < 111 bpm clinical alarm sounds). A CE is considered nonclinically relevant (NCRE) if the newborn is asymptomatic and the event can be explained by a technical problem (insufficient signal capture) or by the newborn’s condition at that moment (crying, newborn handling by the mother, movement, etc.). NCREs do not entail the termination of the intervention.

**Fig. 3 Fig3:**
[figure not shown]
Action protocol when a SO_2_ < 91% clinical alarm goes off

**Fig. 4 Fig4:**
[figure not shown]
Action protocol when a HR > 180 or < 111 bpm clinical alarm sounds

If the CE cannot be explained by any of the above causes, the CE will be considered a CRE depending on whether it occurs for the first or second time, the magnitude of the desaturation, additional heart rate impairment, or if the newborn is symptomatic. A CRE entails the termination of the intervention.

Investigators at the coordinating center will review the compliance with the intervention protocols. If noncompliance is detected, the head of each participating center will be contacted, and the deviations from the protocol will be discussed.

### Outcomes

The main outcome collected in both intervention groups will be the proportion of healthy newborns who undergo at least 1 episode of SO_2_ ≤ 90%.

The following secondary outcomes will also be recorded:The mean SO_2_ level and HR in the first hour, in the second hour, and for both hours combined.The proportion of newborns who undergo at least one episode of SO_2_ ≤ 85%.The proportion of SSC interruption due to a medical indication.The number of HR episodes < 111 bpm and > 180 bpm.The mother’s posture (right lateral decubitus, left lateral decubitus, or supine) and that of her child (right lateral decubitus, left lateral decubitus, supine, or prone) at the time of the episode of SO_2_ ≤ 90% or HR < 111 bpm.

### Participant timeline

The participant timeline is shown in Fig. 5.

**Fig. 5 Fig5:**
[figure not shown]
SPIRIT. Schedule of enrollment, interventions, and assessments

### Sample size and recruitment

We conducted an observational pilot study in the coordinating center. In this study, the mothers performed SSC with their child in the first 2 h postpartum, and there was no intervention on the maternal position adopted. The mothers could choose their position, partially sitting up with an angle between 15° and 50°. We observed that approximately one of every ten healthy newborns had an episode of SO_2_ ≤ 90%.

To calculate the study’s sample size, we predetermined that, with the bed in the 15° and 45° positions, the rate of episodes could be 9% and 6%, respectively. To estimate a reduction of a third in the number of newborns with episodes of SO_2_ ≤ 90% (with a 95% confidence level and a power of 80%), we calculated that we would need to include 1275 newborns in each group, which represented a total of 2550 newborns. In the pilot study, we observed that approximately 50% of the initially included cases had to be excluded due to established postrandomization criteria (see Table 2). Therefore, the estimated number of dyads to randomize would be 5100. We deemed it necessary to include 15% more participants for operational reasons and to conduct an intermediate analysis. The final figure for participants would therefore be 5866.

This number would be easily recruitable among all the centers involved in the study. The recruitment will last 32 months.

### Allocation and blinding

The randomization was conducted using permuted blocks. To this end, we employed a shared computer platform. Each center was assigned a block, and the patients were randomized one after another according to the random numbers contained in the corresponding block. Each center’s block size was created after an initial calculation of the number of mother/newborn dyads the center could recruit over the course of a month (the block sizes ranged from 193 to 1076 cases). The patients will be randomized at the start of labor. Once the informed consent form is signed, the researcher who obtained the consent will access the shared computer platform with the center’s specific login. The platform will then take the researcher directly to their block of random numbers and show them the mother’s degree of inclination. Beforehand, the researcher must answer a series of questions to confirm that the dyad meets all study inclusion criteria and none of the exclusion criteria. The center’s researcher is not allowed to know the block of numbers they are given nor the sequence of numbers. The recorded pulse oximetry data (SO_2_ and HR) will be extracted and analyzed in the coordinating center by researchers who will be blinded to the mother’s sitting angle in bed.

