**Table 2 Tab2:** Postrandomization criteria for withdrawal from the study

*Delivery related*	
(a) caesarean section or instrumental delivery (forceps, vacuum)	
(b) maternal fever > 38 °C	
(c) maternal hemodynamic instability (hypotension, tachycardia, impaired consciousness, poor perfusion, notable pallor) or any other type of ailment	
(d) umbilical cord prolapsed	
(e) signs of fetal “distress”, with fetal scalp pH < 7.25 or umbilical artery pH < 7.20	
(f) any other obstetric complication	
(g) use of sedatives or relaxants during or after delivery	
*Neonate related*	
(a) need for resuscitation measures	
(b) intrapartum-diagnosed major malformation	
(c) Apgar score ≤ 7 at 1, 5, or 10 min	
(d) presence of symptoms before 10 min of life	
(e) birth weight < 2300 g or > 4500 g	

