### Interventions

Before starting patient enrollment, all participating centers have agreed upon the SSC procedure and the study intervention. Additionally, the coordinating center has conducted face-to-face training sessions in each of the hospitals.

When a possible case is identified, consent from the pregnant woman will be requested. Once the woman has agreed to participate, she is shown a number of photographs of how to perform SSC (Fig. 1; “Models for mother’s and newborn’s positions for 15° and 45° inclination”). The woman is told to record the moment(s) when the newborn latches on to the breast. The woman’s data are subsequently entered into the computer platform to proceed with the randomization. After the delivery, the researcher attending the birth will verify that the case does not meet any of the postrandomization withdrawal criteria. The pulse oximetry apparatus (noninvasive Radical-7 Signal Extraction PulseCO-Oximeter® monitor equipped with Masimo Rainbow SET® technology) is then plugged into the power outlet and to the data collection and is subsequently turned on. The pulse oximeter alarms have been established at 91% as the lower limit for SO_2_; the upper limit has not been set. For the HR, the lower limit alarm has been set to 111 bpm and the upper limit to 180 bpm.

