**Fig. 1 Fig1:**
[figure not shown]
Models for mother’s and newborn’s positions for 15° and 45° inclination

During the first 10 min after delivery, with the newborn in SSC, the pulse oximeter sensor is attached (Masimo, LNCS® Series Neo-L adhesive sensor) on the right hand or wrist (preductal SO_2_). Considering the LNCS® sensor directions for use, the precision of the sensors is ± 3% for SO_2_ with or without movement and for the HR ± 3 bpm without movement and ± 5 bpm with movement. The saturation accuracy of the neonate was validated on adult volunteers and 1% was added to account for the properties of fetal hemoglobin. During these first 10 min after birth, the mother’s bed position is changed according to the corresponding randomization group (45° or 15° above the horizontal). To standardize the intervention, two cardboard models (15° and 45°) have been manufactured that exactly reproduce the angle (Additional file 1). During this period, diaper placement is the only intervention allowed.

At 10 min after birth, the sensor cable is attached to the pulse oximeter. After the connection, the pulse oximeter begins continuously recording the HR and SO_2_, storing the data and signal quality every 2 s. The pulse oximeter remains connected to a central station (Patient SafetyNet System, version V.4610, Masimo®) next to the newborn and mother for the 2 h of the study. The system transmits the data to the central station in real-time every second, displaying them on a monitor. The pulse oximeter’s alarms can be silenced and the screen light turned off so as to disturb the mother and newborn as little as possible. The alarms can be silenced in both the monitor and pulse oximeter. The pulse oximeter’s lighting can be reduced to a minimum to disturb the mother and newborn as little as possible. A practitioner is continuously monitoring the display and can respond to an alarm. As a safety mechanism, four locator-searchers (nurse, resident physician, staff physician, and supervising staff physician) provide alerts on the various alarms generated during the recording.

During the intervention period, the newborns remain at all times in SSC with their mother and will not undergo any procedure. If the newborn is separated from their mother for a reason other than those contemplated in the study (see alarm management protocol below), the recording will be stopped and the newborn will be removed from the study.

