### Statistical methods

As we estimate a relevant proportion of estimated postrandomization exclusions, we will perform a modified intention to treat analysis.

The study will employ a two-tailed significance level of 5%. The confidence intervals will be 95%. The main assessment criterion is the presence of an episode of SO_2_ ≤ 90%. We will perform an unadjusted analysis of the intervention’s effect with chi-squared test.

The distribution of the baseline prognostic variables will be analyzed with the mean and standard deviation for the continuous variables (we expect a normal distribution) and with numerators/denominators and percentages for the categorical variables. *P* values will not be included, but we will indicate the variables that have a strong association that could have a confounding effect—even if the distributions in the two study groups are not very different—and the variables with large differences between the groups that could have a confounding effect, even those with a poor association. Stratified analysis and logistic regression modeling will be performed on the primary outcome to take into account covariates (i.e., exploring the possible effect of modification of breast feeding, adjusting for relevant covariates, etc.). The strategies for missing-data imputation and the subgroup analysis will be documented a priori.

The statistical analysis will be conducted using the software environment R [28].

An independent committee, which will include an independent biostatistician, will review the results of the interim analysis.

The study will be halted if differences in the main outcome show a *p* value below 0.001 to protect the overall type I error of the trial. The study will also be interrupted on safety grounds due to any other results that show a negative effect on the child or mother considered relevant by the committee.

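### The assigned angle is known from the start of labor, and unblinded local staff later apply withdrawal criteria that partly rest on judgment, so the modified ITT comparison is open to selection bias through that subset of exclusions

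*Protocol article*

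**What the plan says.** All references are to the protocol article.

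- **Allocation and blinding:** "The patients will be randomized at the start of labor". On disclosure: "The platform will then take the researcher directly to their block of random numbers and show them the mother’s degree of inclination". The only blinding described covers the coordinating-center researchers who extract and analyze the oximetry data.
- **Interventions:** "After the delivery, the researcher attending the birth will verify that the case does not meet any of the postrandomization withdrawal criteria". On the bed: "During these first 10 min after birth, the mother’s bed position is changed according to the corresponding randomization group".
- **Eligibility criteria for participants:** a dyad enters the primary analysis once 10 minutes have passed and no withdrawal criterion has been met.
- **Table 2:** twelve lettered criteria, seven related to delivery and five to the neonate. One of them is "any other obstetric complication".
- **Sample size and recruitment:** in the pilot, "approximately 50% of the initially included cases had to be excluded due to established postrandomization criteria".
- **Statistical methods:** because of these exclusions, "we will perform a modified intention to treat analysis". The primary test is an unadjusted chi-squared test.
- **Data collection, management, and monitoring:** two investigators will independently assess the criteria in a sub-sample, and agreement statistics will be reported.

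**The concern.** Excluding dyads after randomization does no harm if the decision rests on facts that the arm cannot affect and is made without knowledge of the arm. For some Table 2 items neither condition is secured. There are two routes to bias:

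1. **Knowledge of the arm.** The angle is on record from the start of labor and can be seen in the room once the bed is set. A borderline finding can then be read differently in the two arms, even in good faith.
2. **Effect of the intervention.** The background section postulates that maternal inclination can obstruct the newborn's breathing, and early neonatal symptoms are a withdrawal criterion. The discussion leaves open whether inclination affects the mother's state after delivery, and maternal instability is a withdrawal criterion. A withdrawal in the first 10 minutes could therefore be an early effect of the angle, which the analysis would then discard.

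The primary comparison is at stake. Newborns near the margin of these criteria are plausibly the ones more likely to desaturate later. Removing more of them from one arm would shift that arm's event rate.

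**Working it through.** **Step 1. The plan's own figures.** Inputs from the sample-size and statistical sections: 9% versus 6%, two-sided 5%, 80% power.

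- Uncorrected two-proportion formula: n = [1.96·√(2·0.075·0.925) + 0.8416·√(0.09·0.91 + 0.06·0.94)]² / 0.03² = 1209 per arm.
- With continuity correction: (n/4)·[1 + √(1 + 4/(n·0.03))]² = 1275 per arm, as stated.
- 2 × 1275 = 2550; 2550/0.5 = 5100; 5100 × 1.15 = 5865, against the stated 5866.
- Half of 5866 is 2933, so the plan itself expects about 2933 dyads to leave after allocation is known.

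**Step 2. Order of events.**

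| Time | Event | Arm known locally? |
|---|---|---|
| Start of labor | Randomization, angle shown | Yes, to the randomizing researcher |
| After delivery | Birth researcher checks Table 2 | No blinding described |
| First 10 min | Bed set to assigned angle; symptoms, later Apgar scores and maternal state still open | Yes, the bed is visible |
| 10 min | Analysis set fixed, recording starts | Yes |

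**Step 3. Which criteria can be influenced.**

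- *Objective or procedural:* caesarean or instrumental delivery, fever, cord prolapse, fetal distress (tied to pH limits), use of sedatives, major malformation, Apgar cut-off, birth weight.
- *Resting on judgment:* the unspecified maternal ailment at the end of delivery item (c), the unspecified obstetric complication in item (f), and neonatal symptoms in item (d).
- *Partly judgment:* maternal instability in item (c) and the need for resuscitation.

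So four of the twelve lettered items carry some judgment. The documents do not say what share of the 50% they account for.

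**Step 4. Illustration on assumed inputs.** None of these is in the documents except 1275 per arm; 7.5% is the midpoint of 9% and 6%. Assume no true effect, 7.5% risk in both arms, and k extra exclusions with event risk q in one arm only. Expected events are 1275 × 0.075 = 95.625. The remaining rate is (95.625 − k·q)/(1275 − k).

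| k | q | Remaining rate | Spurious shift |
|---|---|---|---|
| 25 | 30% | 88.125/1250 = 7.05% | 0.45 points |
| 25 | 40% | 85.625/1250 = 6.85% | 0.65 points |
| 64 | 30% | 76.425/1211 = 6.31% | 1.19 points |
| 64 | 40% | 70.025/1211 = 5.78% | 1.72 points |

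The counts are 25/1275 = 2% and 64/1275 = 5% of the analyzed arm, or 1.0% and 2.5% of the 2550 randomized per arm. The shift is 0.45/3 = 15% to 1.72/3 = 57% of the planned difference.

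For scale, the standard error of the difference is √(2·0.075·0.925/1275) = 1.04 points. At q = 30%, one-sided extra exclusion of 1%, 2% or 3% of the randomized dyads raises the false-positive rate of the 5% test to about 7%, 15% or 29%.

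**Step 5. The reliability study.** Two raters can agree on every case while exclusions still differ by arm, for example when early symptoms are truly commoner at one angle. Agreement statistics would not show this. The text does not say that the raters are blinded to arm.

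**The case against.** The case on the other side is substantial, and several parts of it stand.

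- **Most criteria are objective.** This stands. A reader might count fetal distress among the open-ended items, but Table 2 ties it to scalp or umbilical artery pH limits.
- **The 50% is not evidence of arm-driven exclusion.** This stands. The pilot was observational, with no intervention on maternal position, so the rate arose without any arm. A reader might infer that half of the sample is selected with knowledge of the arm. The documents support only that the judgment-based subset can be.
- **The same staff need not randomize and exclude.** This stands as a limit on the text: one section speaks of the researcher who obtained consent, another of the researcher attending the birth, and the article does not say whether they are the same person. The exposure remains, because no blinding of the birth researcher is described and the bed angle is visible while some criteria are open.
- **The illustration is assumed.** This stands. Wholly one-sided exclusion and a 30–40% event risk have no source in the documents, and the low end of the range is under half a standard error.
- **Safeguards exist.** In part. Oximetry is device-recorded and analyzed blind, the coordinating center reviews compliance with the intervention protocols, recorded Apgar, pH and weight allow many exclusions to be checked, and adjusted models are planned. None of these conceals the arm at the exclusion decision, and covariate adjustment cannot be relied on to repair selection related to the outcome.
- **The angle cannot be withheld until all of Table 2 is cleared.** This stands. The 10-minute Apgar and symptoms up to 10 minutes are judged after the bed is set. The remedy has to be split by timing.

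**Conclusion.** The concern holds for a subset of exclusions. Allocation is disclosed before eligibility is settled, no blinding is described for those who settle it, and some criteria are both judgment-based and still open once the assigned angle is in place. The primary comparison is therefore open to selection bias, and the reliability study neither prevents nor measures exclusion that differs by arm.

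The documents do not show that bias has occurred, and they give neither its size nor its direction. Extra removal of fragile newborns from the 15° arm would mask a true benefit of 45°; extra removal from the 45° arm would exaggerate or create one. The figure of about 0.45 to 1.7 points against a planned 3 rests wholly on the assumptions in the working. It shows only that a modest imbalance, 1.0% to 2.5% of the randomized dyads in one arm, could matter.

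**What to change.** 1. **Dyads not yet randomized.** Keep consent and registration in labor. Have the platform reveal the angle only after birth, once the researcher confirms on screen that no Table 2 criterion assessable at that time (delivery-related and immediate neonatal items) is met, and before the bed is set. This removes most post-randomization exclusions. Randomizations fall from 5866 toward about 2933 (5866 × 0.5), remaining somewhat above that because later-judged items stay open. The number of consents does not change.
2. **Criteria judged only after the bed is set, and all dyads already randomized.** Have coordinating-center staff blinded to arm adjudicate the judgment-based exclusions from the electronic case report form. Report exclusions by arm and by reason. Add a sensitivity analysis that excludes only on objective criteria and keeps other dyads that have recordings. Dyads withdrawn before recording starts may have no outcome data, so this repair is partial.
3. **Reliability study.** Draw the sub-sample from all randomized dyads, including those excluded, with raters blinded to arm.

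The cost is a protocol amendment, a reordering of screens on a platform that already runs 24 hours a day, one login in the minutes after birth, and the adjudication workload. Enrollment is under way, so step 1 helps only later dyads. No clinical rule needs to change.

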### Data collection, management, and monitoring

In each case, a number of characteristics related to the mother, delivery, and newborn will be recorded (Table 4). These data will be inserted a posteriori in the electronic case report form created for the study and will be accessible for those responsible for the study in the coordinating center. The recorded information corresponding to the SO_2_ and HR for each case will be electronically downloaded through various report formats, which in turn will be submitted to the coordinating center by e-mail. The coordinating center has the appropriate software for reading and analyzing the recorded pulse oximetry data.

**Table 4 Tab4:** Demographic data to be recorded in each case

- *Mother-related*: age, country of origin, medical history of interest, parity, desire to breastfeed, increase in weight during pregnancy, body mass index, bra size (including cup size), a history of children who died, and medication consumed during the 72 h prior to delivery	
- *Delivery-related*: date and time, duration, time of completion, spontaneous or induced, delivery position, epidural anesthesia, time of epidural, time the water broke, nuchal cord, episiotomy, artery and umbilical vein blood gas test, maternal medication during labor and 2 h afterwards.	
- *Neonate-related*: sex, weight, gestational age, Apgar score, cord pH, presence of crying at birth, and time of the first breast latch	

The implementation of post-randomization exclusion criteria will be evaluated in a reliability study. Two investigators will independently assess the criteria in a sub-sample of study participants. Reliability and agreement statistics will be reported.

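### The bed angle is shown at the start of labor, before partly discretionary withdrawal criteria decide who is analysed, so concealment does not protect the primary analysis set

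*Protocol article*

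**What the plan says.** All places are in the Methods of the Protocol article.

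- **Timing and disclosure** (Allocation and blinding): "The patients will be randomized at the start of labor". Once the eligibility questions are answered, "The platform will then take the researcher directly to their block of random numbers and show them the mother’s degree of inclination".
- **When the angle is used** (Interventions, text after Fig. 1): "During these first 10 min after birth, the mother’s bed position is changed according to the corresponding randomization group".
- **Who applies the withdrawal criteria** (Interventions): after delivery, "the researcher attending the birth will verify that the case does not meet any of the postrandomization withdrawal criteria".
- **What they contain** (Table 2): measured or clear-cut items such as mode of delivery, temperature, cord prolapse, pH and birth weight. There are also open-ended ones: "or any other type of ailment", "any other obstetric complication", and symptoms in the first 10 minutes of life, which are not defined.
- **Who is analysed** (Eligibility criteria; Statistical methods): dyads confirmed at 10 minutes to meet none of these criteria, in a modified intention-to-treat analysis.
- **How many are lost** (Sample size and recruitment): in the pilot, "we observed that approximately 50% of the initially included cases had to be excluded due to established postrandomization criteria".
- **Blinding** (Allocation and blinding): stated for the coordinating-center researchers who extract and analyse the oximetry.
- **Planned check** (Data collection, management, and monitoring): a reliability study in which "Two investigators will independently assess the criteria in a sub-sample of study participants".

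**The concern.** Concealment works up to randomization: the center's researcher cannot see the sequence. But entry to the primary analysis is settled later, when the angle has already been displayed. If a borderline dyad is withdrawn more readily in one arm, the two analysed groups are no longer comparable by randomization, even if the angle itself has no effect. Blinded reading of the oximetry cannot repair this, because selection comes before recording. The reliability study measures agreement between two assessors. It does not change who is analysed, and two assessors who lean the same way would agree well. What is at stake is the validity of the primary chi-squared comparison, in either direction.

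**Working it through.** **1. The plan's own figures.** For 9% against 6%, two-sided 5%, 80% power, the pooled-variance formula gives n = [1.96·√(2·0.075·0.925) + 0.8416·√(0.09·0.91 + 0.06·0.94)]² / 0.03² ≈ 1209. The continuity correction, n/4·[1 + √(1 + 4/(n·0.03))]², raises this to 1275 per group, as stated. Then 2 × 1275 / 0.5 = 5100, and 5100 × 1.15 = 5865 (stated 5866). At 50% loss, 5866 × 0.5 = 2933 dyads are analysed, about 1466 per arm.

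**2. Order of events.** Angle displayed at the start of labor; delivery; withdrawal criteria checked and bed set within the first 10 minutes; eligibility confirmed at 10 minutes. Delivery-related items are judged when the arm can be known. Symptoms to 10 minutes and the later Apgar scores can be judged with the bed already in position.

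**3. No true effect, extra withdrawal in one arm.** Assume a 7.5% episode rate in both arms (midpoint of 6% and 9%). A fraction x of otherwise analysable dyads, with episode risk r, is withdrawn in one arm only. That arm's rate becomes (0.075 − x·r)/(1 − x). With k = shift/SE, type I error = 1 − Φ(1.96 − k) + Φ(−1.96 − k). The documents give neither x nor r.

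| x | r | Rate left | Shift (points) | SE (points) | k | Type I error |
|---|---|---|---|---|---|---|
| 1% | 15% | 7.42% | 0.08 | 0.97 | 0.08 | 5.1% |
| 2% | 25% | 7.14% | 0.36 | 0.97 | 0.37 | 6.6% |
| 3% | 40% | 6.49% | 1.01 | 0.95 | 1.06 | 18.5% |

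The last two shifts are 12% and 34% of the planned 3 points. The last row needs staff to remove newborns with 0.40/0.065 ≈ 6 times the risk of the rest, and 0.03 × 0.40/0.075 = 16% of that arm's events, before any recording. Other assumptions (9% base rate, 1275 per arm, withdrawn dyads at 2 to 3 times average risk) give 5.3% to 6.2% for an extra 2%, and 7.0% to 13.5% for an extra 5%.

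**4. True effect as planned, extra withdrawal at 15°.** With 9% against 6% and 1466 per arm, power is 87%. In the second scenario the 15° rate falls to (0.09 − 0.02·0.25)/0.98 = 8.67% and the difference to 2.67 points. With SE 0.97, power = Φ(2.67/0.97 − 1.96) ≈ 79%. In the third, the rate is (0.09 − 0.03·0.40)/0.97 = 8.04% and the difference 2.04 points. With SE 0.95, power is about 57%.

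**5. Would the flow of participants show it?** Withdrawing 1% to 3% of analysable dyads is 0.5 to 1.5 points of those randomized. For total withdrawals, SE = √(2·0.25/2933) = 1.31 points, so p < 0.05 needs about 2.6 points; a true imbalance of 1 to 1.5 points would reach it in only about 12% to 21% of trials. By reason, the test is sharper. If discretionary withdrawals were 2% in one arm and 3% in the other (assumed), SE = √(2·0.025·0.975/2933) = 0.41 points, z = 2.45, p = 0.014. For 5% against 6%, SE = 0.60, z = 1.68, p = 0.09.

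**The case against.** The strongest reply is that the exposure is far smaller than the 50% suggests. Most Table 2 items are objective, and the pilot was observational with no assigned angle, so its loss says nothing about withdrawal influenced by allocation. That stands. A reader might infer that all of the roughly 2933 lost dyads are open to selection; the documents do not support this, because the discretionary share is not given.

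A reader might also infer that delivery staff are known to be unmasked and expect the flatter position to be riskier. Neither is stated. The angle is shown to the researcher who obtained consent, who need not be the one attending the birth. That the latter can know the arm is inferred from the display, from the bed being set within 10 minutes, and from blinding being claimed only for the oximetry work. The hypothesis in the Abstract is the authors' own, and Ethical aspects says there is currently no recommended position.

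Nor do the documents point to a false result in favor of 45°. Readier withdrawal at 15° biases toward no difference. The 18.5% figure needs foresight about which newborns will desaturate that nothing in the text suggests. And it would be too strong to say that an imbalance must stay hidden, since withdrawals by reason could show it.

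The authors did foresee a problem and planned a reliability study. Whether its assessors are masked may be left to a fuller document, so silence there is not held against the plan. What remains is that measuring agreement in a sub-sample does not alter the analysed set.

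**Conclusion.** The weakness is in the stated order of events: allocation is disclosed at a time when it is not yet needed, and entry to the primary analysis is decided afterwards, partly on judgement, by someone not stated to be masked. Concealment before randomization therefore does not protect the analysed set. This does not show that bias will occur. Its size and direction cannot be derived from the documents. Under the assumed one-arm withdrawal of 1% to 3% of analysable dyads, type I error runs from about 5.1%, which is negligible, through 6.6%, to 18.5% in an extreme case; selection at 15° would cost power instead. The point merits a change because disclosure can be moved without touching the intervention, whereas selection that has already happened can be only partly repaired.

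**What to change.** **For further dyads.** Keep consent and the eligibility questions at the start of labor. Have the platform release the angle only after birth, once the attending researcher has entered, with a time stamp, all delivery-related Table 2 items (including the two open-ended ones) and the neonatal items known by then. Symptoms to 10 minutes and later Apgar scores will still follow release, so allocations will somewhat exceed the number analysed. Because enrollment is under way, report results by period before and after the change.

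**For dyads already randomized, and for the late items.** Have the reliability-study investigators judge the discretionary criteria, for withdrawn and retained dyads alike, from records with the angle removed. Tabulate withdrawals by arm and criterion, and bedside against masked decisions by arm. Report a sensitivity analysis of the primary outcome on the set defined by the masked decisions. Dyads withdrawn before monitoring have no recorded outcome, so any that the masked reading would retain need bounds or imputation.

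**Cost.** A platform change, a protocol amendment and one extra log-in shortly after birth, at centers that already have 24-hour access. The masked reading goes beyond the planned sub-sample and takes investigator time; how well the records support it is not stated. No additional women need to be recruited, and no clinical rule changes.
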